### Assessment of Safety

There are no foreseeable risks to the infant or mother. We do not anticipate any adverse effects of the vacuum-triggered trial teat as data from our previous study indicates no change in physiological stability during its use whereby, unlike a conventional teat, milk flow is controlled during feeding. To ensure safety, the incidence of apnoea and bradycardia, and any other adverse effects, will be recorded at each feed and examined at interim analysis when complete data is available for 15 infants in each group.

An expected benefit of study participation is better infant growth (in both infants fed with the conventional teat and those fed with Calmita) because breastmilk transfer will be measured for every breastfeed and top up feeds calculated to meet the volume prescribed by the neonatologist. Currently top up feed volumes are estimated based on assumptions about the volume taken at the breast – data from our previous studies indicate that the assumed volume is frequently overestimated. Mothers in this study may also be encouraged to continue breastfeeding simply due to the monitoring and follow up over the course of the study, whereby breastfeeding duration is tracked; this may result in longer breastfeeding duration.

### Statistical analysis, data management, and record keeping

The primary outcome measure for this study is the total volume transferred during a breastfeed. Meier reported average transfer volumes of  $18.4\text{mL} \pm 13.2$  and  $3.9\text{mL} \pm 7.0$  with and without nipple shield, respectively [11]. Samples sizes required to detect a clinically relevant effect of 5mL difference between feeds with full and empty breasts were calculated separately for these two conditions. The more conservative calculation is that the study would need 24 infants in each treatment group to have 80% power (Type I error rate  $\alpha=0.05$ ) of detecting a difference this large. Allowing for a possible dropout rate of 20%, as was observed in a similar study, 30 infants per group will need to be recruited at 33 weeks CGA. The sample size was calculated as if the data will be analysed using an independent samples *t*-test. Actual analyses will be more powerful, and thus will have power to detect smaller differences.

Using this sample size, an independent samples *t* test would have the power to detect differences in secondary outcomes equivalent to  $0.83 * \text{SD}$ . This is equivalent to differences of approximately 3.9 min total sucking duration, and 12 suck bursts per feed. As with the primary outcome, use of covariate data, repeated measurements and more powerful analytic techniques increase the likelihood of detecting smaller differences than those determined here.

Data will be analysed on an intention to treat basis using R 2.15 or later versions (The R Core Team)[12] with nlme,[13] lattice,[14] and multcomp[15] packages for linear mixed models, graphical exploration and general linear hypothesis tests, respectively. To monitor both safety and efficacy, interim analysis will be performed when complete data is available for 15 infants in each group, with p values set to  $p=0.029$  for both interim and final analyses as per Pocock (p372, [16]).

For the monitored breastfeeds, differences in milk transfer volume as well as measured sucking, physiological, and feeding variables, linear mixed effects modelling will be used, with grouping for the random effects at the participant level. Use of nipple shield (yes/no), breast fullness (full/empty) and relevant demographic variables will be considered as predictive factors.

Paper records of data will be stored in a locked filing cabinet within a locked room at the Neonatology Clinical Care Unit (NCCU). Electronic data records will be backed up and both copies stored in password-protected files on a lap top computer.

Study investigators will transport re-identifiable milk samples from KEMH to the laboratories of the School of Chemistry and Biochemistry at The University of Western Australia where they will be secured in frozen storage at  $\leq -20^{\circ}\text{C}$  until the time of analysis.

Access to paper records and electronically stored data will be strictly limited to the study investigators. They will be securely stored for 15 years after publication of findings, after which time paper records will be shredded and electronic data will be overwritten.

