### Trial Design

#### Trial endpoints

The primary endpoint for this trial is total breastfeed volume (mL) transferred at a breastfeed, measured at 33, 34, 35 weeks and term CGA

Secondary endpoints to be measured during monitored feeds are  
efficiency (mL/min)

- total suck duration

- total suck bursts
- mean, peak and baseline intraoral vacuum (mmHg)
- oxygen saturation range
- heart rate range
- incidence of bradycardia
- incidence of oxygen desaturation

The following feeding endpoints will also be determined

- timing of achievement of full oral feeds
- timing of achievement of full breastfeeding
- breastfeeding duration (monitored up to 3 months post-term)

1. A randomized controlled clinical trial will be undertaken with random allocation in blocks of size 4 to either a control group or an intervention group. Study design is depicted in Figure 1.
2. A pilot study of up to 5 infants will be completed prior to commencement of the trial to test and refine the set-up and duration of monitoring sessions.
3. Study participant data and milk samples will be re-identifiable, with an identification code assigned to each infant. A master sheet that matches infant identity to identification codes will be stored in a password-protected electronic file on a lap top computer. All paper copies of case report forms will be stored in a locked filing cabinet at The University of Western Australia.
4. The effect of a vacuum-controlled bottle-feeding teat (Calmita and Calma teats, Medela AG) on breastfeeding outcomes will be evaluated in this clinical trial. A shut-off valve is incorporated into the Calmita teat so milk flows only when the infant creates a vacuum. Venting prevents collapse of the teat. There are two versions of Calmita with different threshold levels for the vacuum-controlled valve of  $-10 \pm 5$  mmHg (starter teat) and  $-30 \pm 15$  mmHg (advanced teat). We have previously investigated a prototype of this product but wish to carry out more extensive studies on the final product.

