## Treatment of Participants

1. When the mother is not available to breastfeed, control group infants will use a conventional teat for suck feeds whereas the interventional group infants will use the Calmita teat. The starter teat will be offered initially and when the infant takes full feeds from the starter teat for 48-72 hours they will then use the advanced teat.
2. Monitoring of a weekly breastfeeds and bottle feeds with the allocated teat will be performed at 33, 34 and 35 weeks CGA and involves the following
  - Weigh infant pre and post breastfeeding
  - Intraoral ultrasound
  - Continuous Intraoral vacuum measurements
  - Respiratory Inductive plethysmography
  - Continuous pulse oximetry for oxygen saturation (SaO2) and heart rate
  - (optional) Maternal pre/post breastfeed milk samples <1.0mL
  - Maternal rating of Preterm Infant Breastfeeding Behavior Scale[5] (PIBBS, Appendix A)

SSB coordination is evaluated using data from intraoral vacuum, respiration and swallowing (Respiratory Inductive Plethysmography) heart rate and oxygen saturation obtained throughout the entire breastfeed[6].

3. Test weights of the infant pre and post feed, for all feeds, will be made to determine milk intake and allow calculation of top up feeds. For monitored feeds, pre and post feed milk samples (<1.0mL) will be collected and fat content measured to provide a further estimate of breast fullness.
4. At each monitored breastfeed the Preterm Infant Breastfeeding Behavior Scale[5] (PIBBS, Appendix A) will be completed by the mother.
5. In the study setting it is assumed that most stable preterm infants are offered (at least daily) breastfeeding experiences from 32 weeks CGA. A weekly breastfeed will be monitored from 33 weeks CGA. At 34 weeks CGA each infant will have up to 2 breastfeeds and one bottle-feed monitored in random order on 2-3 consecutive days with a full or empty breast. A full breast is one that has not been expressed for 3 hours prior to feeding and an empty breast one that has been expressed within an hour of the feed. At 35 weeks CGA those using a nipple shield will have the option of also having a monitored breastfeed without a nipple shield.
6. At 35 weeks or at discharge/transfer each infant will have 1 breastfeed monitored with or without a nipple shield depending on whether the infant is typically feeding with a shield, and one bottle-feed will be monitored. Infants

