### Assessment of Efficacy

Efficacy of the trial teat will be evaluated through measurement of the primary endpoint ie. total volume transferred at the breast, and secondary endpoints that relate to breastfeeding outcomes (eg. volume transferred per minute, range and average intraoral vacuum, achievement of full oral feeds, full breastfeeding and breastfeeding duration) and safety (eg. SSB coordination and incidence of apnoea and bradycardia during feeding). To assess efficacy, total volume transferred at the breast will be examined at interim analysis when complete data is available for 15 infants in each group, and again on completion of the study.

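### The 80% power for 5 mL is for full versus empty breast, a within-infant contrast, but it is stated per teat arm; the teat comparison on the primary endpoint has no power figure

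*Combined protocol and SAP*

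**What the plan says.** Under Trial endpoints, the design is "random allocation in blocks of size 4 to either a control group or an intervention group". Treatment of Participants, item 1, defines the groups: "control group infants will use a conventional teat for suck feeds whereas the interventional group infants will use the Calmita teat". Assessment of Efficacy ties the teat to the primary endpoint: "Efficacy of the trial teat will be evaluated through measurement of the primary endpoint ie. total volume transferred at the breast".

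The section on statistical analysis sizes the study on a different contrast, "a clinically relevant effect of 5mL difference between feeds with full and empty breasts were calculated separately for these two conditions", and concludes: "The more conservative calculation is that the study would need 24 infants in each treatment group to have 80% power". After 20% dropout, "30 infants per group will need to be recruited at 33 weeks CGA". It states that an independent samples t-test was assumed and that the real analyses will have more power. It then gives a detectable difference of 0.83 SD for secondary outcomes without naming the contrast. Interim and final tests are set at p = 0.029.

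Full and empty feeds are not separate groups of infants. Treatment of Participants, item 5, has "each infant will have up to 2 breastfeeds and one bottle-feed monitored in random order" at 34 weeks, from a full or an empty breast. Table 1 schedules both feeds at that age and does not distinguish the arms.

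**The concern.** Two contrasts share one endpoint. The teat comparison is between infants, and its sample size is a number per arm. The fullness comparison is within infant, with the arms pooled, and its sample size is a total number of pairs. The plan takes its effect size from the second and expresses the answer in the units of the first, so the figure of 24 per group describes neither.

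The teat is the randomised intervention, and it is examined for efficacy at an interim and a final look. If the teat result is null, the only primary-endpoint power figure to set beside it is 80% for 5 mL, which was never calculated for the teat.

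**Working it through.** **Inputs from the statistical analysis section.** Target 5 mL; SD 13.2 mL with a nipple shield and 7.0 mL without; 80% power; alpha 0.05 for sizing and 0.029 for testing; 24 evaluable infants per group. Two-sided testing is assumed. It fits the 0.83 SD statement, since 24 per group gives 0.826 SD two-sided and 0.73 SD one-sided.

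**Inputs not in the documents.** The correlation between feeds from one infant is assumed to be 0.3, 0.5 or 0.7. No teat effect is given, so 5 mL is used for illustration only.

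**1. The plan's own figure.** The dropout step reproduces: 24 / 0.8 = 30. The 24 does not. An independent t-test for 5 mL needs 32 per group at SD 7.0 and 111 at SD 13.2. A requirement of 24 implies an SD of 5 / 0.826 = 6.05 mL, which the documents do not give. That is a separate matter; here it means only that detectable differences must be worked from the quoted SDs.

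**2. Teat, 24 v 24, one feed per infant.** Detectable difference = d × SD, with d = 0.826 at alpha 0.05 and 0.897 at 0.029 (exact t-test, 80% power).

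| SD | Detectable, 0.05 | Detectable, 0.029 | Power for 5 mL, 0.05 | Power for 5 mL, 0.029 |
|---|---|---|---|---|
| 7.0 | 0.826 × 7.0 = 5.8 mL | 0.897 × 7.0 = 6.3 mL | 68% | 59% |
| 13.2 | 0.826 × 13.2 = 10.9 mL | 0.897 × 13.2 = 11.8 mL | 25% | 18% |

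**3. Teat, mean of four feeds.** The endpoint is measured at 33, 34 and 35 weeks and at term. With a constant teat effect and common correlation ρ, the SD is multiplied by √((1 + 3ρ)/4), which is 0.689, 0.791 and 0.880 for ρ = 0.3, 0.5 and 0.7. At alpha 0.029:

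- SD 7.0: 6.28 × these factors = 4.3, 5.0 and 5.5 mL.
- SD 13.2: 11.84 × these factors = 8.2, 9.4 and 10.4 mL.

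Power for 5 mL in the same order at SD 7.0 is 94%, 87% and 79% at alpha 0.05, and 91%, 81% and 71% at 0.029. At SD 13.2 it is 46%, 37% and 31% at alpha 0.05.

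**4. Fullness, paired, arms pooled.** At most 2 × 24 = 48 pairs. SD of the difference = SD × √(2(1 − ρ)); detectable difference = 0.413 × that SD (paired t-test, alpha 0.05, 80% power).

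| SD | ρ | SD of difference | Detectable | Power for 5 mL |
|---|---|---|---|---|
| 7.0 | 0.3 | 8.28 | 3.42 mL | 98% |
| 7.0 | 0.5 | 7.00 | 2.89 mL | above 99% |
| 7.0 | 0.7 | 5.42 | 2.24 mL | above 99% |
| 13.2 | 0.3 | 15.62 | 6.45 mL | 58% |
| 13.2 | 0.5 | 13.20 | 5.45 mL | 73% |
| 13.2 | 0.7 | 10.22 | 4.22 mL | 91% |

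**The case against.** The plan says openly that the independent-samples calculation is a simplification and that the actual analysis will do better. It names full and empty breasts in the sizing sentence, so a careful reader is not told that 5 mL is a teat effect. It plans linear mixed models with participant-level random effects and credits repeated measurements and covariates. It also gives a detectable difference of 0.83 SD, which matches 24 v 24.

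Much of this stands. Repeated feeds can raise power for the teat: at SD 7.0, four feeds give 79% to 94% for 5 mL at alpha 0.05. A reader might infer that the teat is necessarily worse powered than stated and fullness better. The documents support neither. The teat result depends on the SD, the correlation and how many feeds count. Fullness falls below 80% for 5 mL at SD 13.2 with correlations of 0.3 and 0.5. Nor can it be said that the plan contains no between-group power statement at all, because the 0.83 SD sentence can be read as one for secondary outcomes.

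What the objection does not supply is a teat effect or power on the primary endpoint. A declared stand-in for the fullness contrast does not become a calculation for the teat. The gain from repeated feeds rests on assumptions that the plan does not state, and the sentence listing the mixed model's predictive factors names shield, fullness and demographics but not teat arm.

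**Conclusion.** The point holds in this form: the stated power belongs to a within-infant contrast, is computed as if between infants and is reported per teat arm. The randomised teat comparison has no effect size or power on the endpoint used to judge it.

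At alpha 0.029 and 24 per arm, the teat difference detectable with 80% power runs from 4.3 mL (SD 7.0, four feeds, correlation 0.3) to 11.8 mL (SD 13.2, one feed). The four-feed figures assume a constant effect, equal correlation and no missing feeds. The fullness figures assume 48 complete pairs, which is an upper bound because the plan allows "up to 2 breastfeeds and one bottle-feed monitored in random order on 2-3 consecutive days", so some infants may give only one breastfeed. The correlations are assumptions throughout.

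A reader might also infer that the trial was sized by feasibility for the teat. No section says so, and that rationale should not be attributed to the plan.

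**What to change.** Replace the single power statement with two.

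- **Teat, between arms.** Give the detectable difference for 24 v 24 at the level actually used, 0.029: 6.3 mL (SD 7.0) to 11.8 mL (SD 13.2) for one feed. If repeated feeds are to be credited, state the number of feeds, the constant-effect assumption and the correlation; with four feeds and correlations of 0.3 to 0.7 the range is 4.3 to 5.5 mL (SD 7.0) or 8.2 to 10.4 mL (SD 13.2).
- **Fullness, paired within infant, arms pooled.** Base it on at most about 48 pairs and state the SD, the assumed correlation and the alpha. The figures in step 4 are for 0.05; if 0.029 is meant to govern this test too, the multiplier rises from 0.413 to 0.448.

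Do not apply the 80% for 5 mL claim to the teat, and say that the 0.83 SD figure refers to secondary outcomes and to which contrast. The cost is protocol wording: no extra infants and no change in conduct. The stated teat figure may become less favourable than the one readers now see.

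### The 24 infants per group for 80% power to detect 5 mL cannot be reproduced from the plan's stated inputs, and the plan does not make clear which contrast the figure is for

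*Combined protocol and SAP*

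**What the plan says.** All the inputs stand in the combined protocol and SAP, under Statistical analysis, data management, and record keeping.

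- The primary outcome is the volume transferred at a breastfeed. A cited study of nipple shields supplies the variability: SD 13.2 mL with a shield and 7.0 mL without.
- The target is a "clinically relevant effect of 5mL difference between feeds with full and empty breasts". Sample sizes "were calculated separately for these two conditions", which I read as with and without a shield.
- The result is "The more conservative calculation is that the study would need 24 infants in each treatment group to have 80% power" at a type I error rate of 0.05. Allowing for 20% dropout, this becomes 30 per group.
- On method: "The sample size was calculated as if the data will be analysed using an independent samples" t-test. The plan adds that the actual analyses will be more powerful, but gives no figure for the gain.
- The next paragraph says that a t-test with this sample "would have the power to detect differences in secondary outcomes equivalent to" 0.83 SD.
- The interim and final analyses are each tested at p = 0.029.

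Treatment of Participants (item 5) and Table 1 schedule the full-breast and empty-breast feeds in the same infant at 34 weeks. Assessment of Efficacy makes volume transferred at the breast the measure of efficacy for the trial teat, which is a comparison between randomised arms.

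**The concern.** The paragraph gives enough to repeat the calculation, and the answer is not 24 for either SD. Of two calculations that differ only in SD, the cautious one uses the larger SD, and with 13.2 mL the requirement is several times 24.

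This is the plan's only justification of its sample size. Anyone who relies on the 80% figure, for example when interpreting a null result on the primary outcome, would be relying on a number that the inputs do not support. The plan does not say how a null result will be read, so that consequence is a risk and not something the plan commits to.

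A second difficulty lies beneath the first. The 5 mL belongs to one contrast (full versus empty breast) and the group size to another (Calmita versus conventional teat). No target difference is stated for the teat comparison.

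**Working it through.** **Inputs.** Difference 5 mL; SD 7.0 or 13.2 mL; alpha 0.05; power 80%; independent-samples t-test; equal groups. Sidedness is not stated and is inferred in step 2.

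**1. The plan's figure.** The normal approximation is n per group = 2 × (1.960 + 0.842)² × SD² / 5², with (1.960 + 0.842)² ≈ 7.85.

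- SD 7.0: 2 × 7.85 × 49 / 25 ≈ 30.8, so 31. The exact t-test gives 31.8, so 32.
- SD 13.2: 2 × 7.85 × 174.24 / 25 ≈ 109.4, so 110. The exact t-test gives 110.4, so 111.

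Neither is 24. The dropout step does reproduce: 24 / (1 − 0.20) = 30.

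**2. Sidedness.** With 24 per group, 80% power and alpha 0.05, the detectable difference is 0.826 SD two-sided and 0.729 SD one-sided. The plan's 0.83 SD matches the two-sided value. For 24 per group to detect 5 mL, the SD would have to be 5 / 0.826 = 6.05 mL, which the plan does not quote.

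**3. Other routes to 24.**

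| Calculation (80% power, 5 mL) | SD 7.0 | SD 13.2 |
|---|---|---|
| Independent t, two-sided 0.05 | 32 per group | 111 per group |
| Independent t, one-sided 0.05 | 25 per group | 87 per group |
| Paired t, SD of differences equal to the quoted SD | 18 infants | 57 infants |
| Paired t, correlation 0.3 | 24 infants | 79 infants |

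The one-sided SD 7.0 result (25) is close, but it conflicts with the 0.83 SD statement and uses the smaller SD. The paired result of 24 needs a correlation that the plan does not give. It would also be a total number of infants, not a number per group, and the plan names an independent-samples test.

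**4. Power of an independent t-test for 5 mL, one feed per infant, two-sided.**

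| | SD 7.0 | SD 13.2 |
|---|---|---|
| 24 per group, alpha 0.05 | 68% | 25% |
| 24 per group, alpha 0.029 | 59% | 18% |
| 30 per group (no dropout), alpha 0.05 | 78% | 30% |
| n per group for 80% at 0.029 | 38 | 129 |
| Difference detectable at 80%, n = 24, alpha 0.05 | 0.826 × 7.0 = 5.8 mL | 0.826 × 13.2 = 10.9 mL |
| Difference detectable at 80%, n = 24, alpha 0.029 | 0.897 × 7.0 = 6.3 mL | 0.897 × 13.2 = 11.8 mL |

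The 0.029 rows are for the final test alone. Counting a possible rejection at the interim look raises power somewhat, but not above the 0.05 row.

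**5. Full versus empty breast within infant.** The SD of the within-infant difference is SD × √(2(1 − ρ)), where ρ is the correlation between an infant's two feeds. The documents give no ρ, so the values below are assumptions. I also assume that 48 completers (24 + 24) each give both feeds.

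| ρ | SD 7.0: power at 0.05 / 0.029 | SD 13.2: power at 0.05 / 0.029 |
|---|---|---|
| 0 | 93% / 89% | 44% / 35% |
| 0.3 | 98% / 97% | 58% / 49% |
| 0.5 | over 99% / over 99% | 73% / 65% |

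At SD 13.2, 80% power needs ρ of about 0.58 at 0.05, or about 0.64 at 0.029.

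**6. Repeated feeds in the between-arm comparison.** The primary endpoint is measured at four ages. Averaging four uncorrelated feeds, the most favourable non-negative correlation, divides the variance by four. At SD 13.2 and 0.05 the requirement is then 109.4 / 4 = 27.4, so 28 per arm, still above 24 if no covariate gain is assumed. At SD 7.0 a smaller gain would do: the variance would need to fall to 24 / 31.8 = 0.76 of its single-feed value at 0.05, or 24 / 37.1 = 0.65 at 0.029.

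**The case against.** The strongest reply is that the t-test is only a planning device. The plan says so, expects its mixed models to do better, and attaches the 5 mL to a contrast that each infant supplies in full. For that contrast at SD 7.0, power exceeds 80% for any non-negative correlation, even at 0.029.

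This stands, and it limits the point. A reader might infer from 68% and 25% that the trial as a whole lacks its stated power. The documents do not support that, because those figures belong to a comparison of independent groups on one feed per infant. The reply does not rescue the figure of 24, however. The plan says how 24 was obtained, and that method does not give it. Nor does the reply settle the cautious case: at SD 13.2 the within-infant contrast reaches 80% only with a fairly high correlation, and the plan assumes none. Pairing full and empty feeds also does nothing for the comparison of teats.

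Two further cautions are fair. The 0.83 SD statement concerns secondary outcomes and is simply the detectable effect at 24 per group, so turning it into millilitres restates the discrepancy and does not add a second one. Its use here is to show that the calculation was two-sided. And because sidedness is not stated, a one-sided calculation at SD 7.0 may be where 24 came from. Even so, that would not be the more cautious result.

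**Conclusion.** The point holds as an error in the stated derivation. On the plan's own method the requirement is 32 or 111 per group, not 24. The stated t-test has 68% or 25% power at 24 per group, or 59% or 18% at the level the plan will actually use. This rests on the two quoted SDs, a two-sided test and equal groups.

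The shortfall is shown for that t-test and for a between-arm comparison of single feeds. It is not shown for every planned analysis: the full-versus-empty contrast may be well powered at SD 7.0, and at SD 13.2 the answer depends on a correlation that the plan does not state. What is missing is one clear account of which contrast, SD, sidedness, test level and correlation support the sample size.

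**What to change.** Keep 30 recruited per arm. Remove the description of 24 as the more cautious result, and restate power by contrast:

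- **Between teat arms.** With 24 completers per arm, one feed per infant, an independent t-test at two-sided 0.029 has 80% power for about 6.3 mL if the SD is 7.0 mL, or 11.8 mL if it is 13.2 mL. Power for 5 mL is 59% or 18% (68% or 25% at 0.05). Any gain claimed from repeated feeds or covariates should be shown with its assumptions.
- **Full versus empty breast, within infant.** Report paired or mixed-model power at 0.029 with the assumed correlation stated. For example, 48 infants giving both feeds have at least 89% power for 5 mL at SD 7.0 for any non-negative correlation. At SD 13.2 power is about 35% at correlation 0 and 65% at 0.5.

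The plan should also say which contrast the 5 mL target is meant for. If a different SD or a paired calculation lay behind the 24, it should be disclosed.

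The cost is wording only, with no change to recruitment or procedures. The downside is that the stated power becomes less favourable.

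### Sample size and the 0.83 SD detectable difference are computed at alpha 0.05, but testing is at 0.029 at both looks, so power at 0.83 SD is about 75%, not 80%

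*Combined protocol and SAP*

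**What the plan says.** All the sizing statements are in 'Statistical analysis, data management, and record keeping'.

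- **Primary outcome.** The target is a "clinically relevant effect of 5mL difference between feeds with full and empty breasts". The plan concludes that "the study would need 24 infants in each treatment group to have 80% power", at a type I error rate of 0.05. A 20% dropout allowance takes 24 to 30 recruited per group.
- **Test assumed.** "The sample size was calculated as if the data will be analysed using an independent samples *t*-test". The plan adds that the real analyses will be more powerful, without giving a figure.
- **Secondary outcomes.** With this sample size a t-test "would have the power to detect differences in secondary outcomes equivalent to" 0.83 SD, which the plan translates to roughly 3.9 min of sucking and 12 suck bursts.
- **Interim.** The next paragraph plans an interim analysis of safety and efficacy at 15 infants per group with complete data, and sets p=0.029 "for both interim and final analyses as per Pocock".

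'Assessment of Efficacy' confirms that the primary endpoint, total volume transferred at the breast, is examined at the interim and again on completion. No passage says that the sample size or detectable difference was adjusted for the lower level.

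**The concern.** A test at 0.029 is harder to pass than a test at 0.05, so with the number of infants fixed it has less power. The plan gives its power and detectable difference at one level and tests at another. The stated figures therefore describe a test that will not be run. The gap exists whatever SD is used for milk transfer.

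The validity of a positive result is not at stake. What is affected is the justification for enrolling 60 preterm infants and the reading of a null result: the trial would appear able to exclude smaller differences than it can.

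**Working it through.** **Inputs, all from the statistical section:** 24 evaluable per group; 80% power; alpha 0.05 for sizing; 0.029 at each of two looks; interim at 15 per group; SDs of 7.0 mL (no shield) and 13.2 mL (shield); target 5 mL; dropout 20%. Sidedness is not stated. Two-sided is assumed because it reproduces the plan's 0.83 SD; one-sided at 0.05 would give 0.73 SD.

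**Formula.** For a two-sample t-test with n per group and standardised difference d, the noncentrality is d × √(n/2) on 2n − 2 degrees of freedom. Power is the probability that this noncentral t exceeds the two-sided critical value in absolute size.

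**Step 1: reproduce the plan.** With n = 24 and d = 0.83, noncentrality = 0.83 × √12 = 2.875 on 46 df. At alpha 0.05 the critical value is 2.013 and power is 80.4%. The difference detectable at 80% is 0.826 SD. Solving for n at 0.83 SD gives 23.8, so 24, and 24/0.8 = 30. The 0.83 SD figure therefore comes from alpha 0.05 with no interim adjustment.

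**Step 2: final test alone at 0.029.** The noncentrality is still 2.875, but the critical value is 2.254. Power is 73.1%, and the difference detectable at 80% is 0.897 SD.

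**Step 3: two-look design for the primary endpoint.** Rejection can occur at either look, so interim rejections count. Simulated t-tests at 15 and then 24 per group, each at 0.029:

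| True difference | Probability of rejecting at either look |
|---|---|
| 0 | 4.7% |
| 0.83 SD | 75.5% |
| 0.875 SD | about 80% |
| 0.88 SD | 80.5% |

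The first row is the overall type I error, and it is below 0.05. With the final look at 30 per group it is 4.9%.

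**Step 4: secondary outcomes in natural units.** The implied SDs are 3.9/0.83 = 4.7 min and 12/0.83 = 14.5 bursts. At 0.897 SD these become 4.7 × 0.897 = 4.2 min and 14.5 × 0.897 = 13 bursts.

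**Step 5: the 5 mL target.** In SD units, 5/7.0 = 0.71 and 5/13.2 = 0.38. Power of a single independent t-test at n = 24:

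| SD | alpha 0.05 | alpha 0.029, final test only |
|---|---|---|
| 7.0 mL | 68% | 59% |
| 13.2 mL | 25% | 18% |

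The 80% claim for 5 mL thus fails at 0.05 already, before the change of level. The step from 80% to about 75% applies to an effect of 0.83 SD, not to 5 mL.

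**The case against.** **The threshold is correct.** A reader might infer from two different alphas that the error rate is uncontrolled. The documents do not support that: 0.029 per look is the Pocock level for an overall 0.05, and the calculation gives about 0.047. The stated 0.05 is right as an overall rate. This stands; only the power figures are at fault.

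**The final-look figures overstate the loss for the primary endpoint.** It is tempting to quote 73% and 0.90 SD throughout. But the primary endpoint is tested twice, so its power includes interim rejections. The loss is about 5 points, not 7. This stands, and 73% and 0.90 SD are used here only for outcomes tested once at 0.029.

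**Secondary outcomes may not be tested at 0.029.** 'Assessment of Efficacy' names only total volume for the interim efficacy look, and the statistical section neither includes nor exempts the other outcomes. A reader might infer that 3.9 min and 12 bursts are wrong. That follows only if 0.029 covers them; if they are tested once at 0.05, they stand. Even then the change is small: 0.3 min and one burst.

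**The real analysis is a mixed model.** The plan calls the t-test a simplification and expects gains from covariates and repeated measurements. Offsetting the final-look loss needs a variance reduction of about 15%, since (0.826/0.897)² = 0.85. A covariate correlation of about 0.39 would do that (0.39² = 0.15), but this is an assumption, because the documents give no correlation. The point makes the loss less serious. It does not make correct a figure stated for an independent t-test.

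**Thirty per group are recruited.** With no dropout, power at 0.83 SD is 83% even on the final test at 0.029. But the plan itself expects 20% loss and rests its claim on 24.

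**Conclusion.** The mismatch is real and moderate. For an independent t-test with looks at 15 and 24 per group, each at two-sided 0.029, overall power for the primary endpoint at 0.83 SD is about 75%, and the difference detectable at 80% power is about 0.88 SD. For an outcome tested only at the end at 0.029, the figures are 73% and 0.90 SD (about 4.2 min and 13 bursts). These rest on two-sided testing, 24 evaluable per group and no credit for the mixed model.

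A reader might also infer that enrolment must rise, or that settling the significance level restores 80% power for 5 mL. Neither follows. The figures can be stated honestly at the planned size, and the 5 mL claim has a separate and larger fault in its SDs. Severity is should-fix, handled together with the correction to the 5 mL calculation.

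**What to change.** Choose one of two routes. Neither changes enrolment.

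- **(a) Keep the interim efficacy test and restate the figures.** For the primary endpoint, give about 75% power at 0.83 SD and about 0.88 SD detectable at 80%. For secondary outcomes, state the level: if 0.029, give 0.90 SD, about 4.2 min and 13 bursts; if they are tested once at 0.05, say so and keep 0.83 SD, 3.9 min and 12 bursts. The cost is a few words and a less favourable figure.
- **(b) Drop the interim efficacy test**, keep the interim safety review already described in 'Assessment of Safety' and in the criteria for termination, and test at 0.05, where 0.83 SD is correct. The cost is the early efficacy look.

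Under either route, state that tests are two-sided and correct the claim of 80% power for 5 mL separately, because changing alpha alone does not repair it.
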